### Data management

A site supervisor reviews all data collection forms for completeness and protocol deviations and/or violations before sending them to the data management center at ICDDR,B on a weekly basis. Electronic (scanned) versions of all forms are also regularly saved for long-term storage. The database was designed using SQL Server 2008 and data are entered using Visual Studio 2010 (both from Microsoft, Redmond, WA, USA). A set of range and consistency checks are built into the data capture system to provide immediate feedback to data entry personnel regarding errors or inconsistent data. Double data entry is used to further reduce the rate of date entry errors.

### Outcome measures

The primary trial outcome measure is LAZ at 1 year of age, where *length* refers to an infant’s fully extended crown-to-heel distance in the supine position. Growth faltering in resource-poor settings primarily occurs early [7], and any effects of the intervention are expected to be apparent by 1 year of age. Our preliminary trial data revealed a discernible effect of prenatal vitamin D supplementation on infant LAZ at 1 year [26]. Because some infants might not be reached at exactly 1 year of age (52 weeks), measurements taken up to 60 weeks will be included in the primary 1-year outcome analysis, implying a range of 364–420 days. LAZ based on WHO growth standards will be used to account for sex imbalances between groups and variance in exact age at the time of measurement. Infant follow-up will continue to 2 years of age (with continued treatment masking) to establish the persistence of effects, to capture potential catch-up growth, and because stunting prevalence does not stabilize until 18–24 months of age [7]. To improve uniformity with respect to the timing of the 2-year visit, it will be scheduled at 24 months of age (104 weeks) but may be completed up to 27 months of age.

LAZs and z-scores for weight for age (WAZ), weight for length (WFLZ), and head circumference for age (HCAZ) will be calculated according to the sex-specific WHO growth standards (WHO-GS) [54, 55] using the STATA igrowup package (http://www.who.int/childgrowth/software/en/). Extreme z-scores will be flagged by the WHO Anthro software (less than −6 SD or greater than 6 SD for LAZ, greater than 5 or less than −6 for WAZ, greater than 5 or less than −5 for HCAZ, and greater than −5 or less than 5 for WFLZ). These extreme values will be manually reviewed to ensure they are not the result of data recording or entry errors. Real values that are extreme low outlying z-scores are expected to be contributed primarily by infants who had early preterm births and of very low birth weight. Other secondary growth outcomes (UAL, MUAC, and RKL) and postnatal growth velocity will be analyzed using raw values or age- and sex-standardized z-scores based on WHO standards (except for RKL).

### Statistical analysis

For the primary trial efficacy outcome analysis, mean LAZ (at 1 year of age) will be compared across groups using analysis of variance. To assess the effect of prenatal vitamin D on mean LAZ at 1 year of age, we plan to perform five primary between-group analyses: each prenatal vitamin D dose versus placebo (three pairwise comparisons), as well as comparisons between all adjacent vitamin D doses (two pairwise comparisons). Because the primary hypotheses relate to differences between two groups, each analysis will be akin to an independent-samples *t* test. The primary effect measure for each comparison will be expressed as a mean difference between groups with 95 % CI. However, an overall α for statistical significance for all five comparisons will be 0.05 (two-sided), and the Holm test will be used to account for multiple testing. Therefore, even if the 95 % CI for a particular mean difference does not include zero, it is possible that it may not be considered statistically significant when all five comparisons are presented together. The postpartum effect analysis will be the comparison of mean LAZ at 1 year of age between infants of mothers who received 28,000 IU/wk versus placebo in the postpartum period (among women who received 28,000 IU/wk prenatally), using a statistical approach similar to that described for the prenatal effect analysis. The nominal αfor statistical significance will be 0.05 (two-sided test) for this analysis. Because there is only one primary pairwise comparison related to the postpartum effect, no adjustment for the multiplicity of outcomes is planned.

In the primary analyses, an intention-to-treat (ITT) approach will be used, meaning participants will be considered exactly as randomized, regardless of supplementation adherence or completeness of follow-up and without adjustment for baseline covariates, and also without imputation for missing data; that is, infants for whom LAZ is unavailable at 1 year of age will be excluded from the analysis. However, because the trial is aimed at establishing a biological mechanism of effect, per-protocol analyses will also be performed by restricting to participants who consumed at least 90 % of all scheduled doses. Conventional ITT analyses of postnatal growth outcomes typically disregard between-individual variations in GA at birth; however, because the WHO-GS was based on a full-term cohort [54], this may lead to differential misclassification of preterm infants with respect to LAZ if length is plotted on the growth chart using the chronological age. Although we plan to follow the convention in the primary analysis, we will perform a sensitivity analysis in which LAZ will be assigned to preterm infants using the age corrected for GA at birth (rather than chronological age). Several other sensitivity analyses are planned. Multivariable adjustment will be used for covariates that substantially differ across groups at baseline. A missingness analysis will be performed to understand the pattern of missing data (in particular to detect differential loss of data across groups), and multiple imputation methods will be used in sensitivity analyses to correct for these losses. Subgroup and interaction analyses will be based on the following covariates: GA at birth, infant sex, maternal baseline vitamin D status, maternal height, and maternal supplement adherence.

Two secondary approaches will be used to examine the effects of vitamin D on linear growth. Regression spline models, with knots at the major scheduled follow-up visit time points, will be used to analyze changes in mean LAZ over discrete time intervals. Interaction terms for time and group allocation will be used to test between-group differences in the changes in LAZ during discrete time intervals. As well, participants will be classified as “stunted” if LAZ is less than −2, and both cross-sectional and longitudinal comparisons will be undertaken to assess the relative risks of stunting across groups. In longitudinal analyses of LAZ or stunting described above, generalized estimating equations with robust variance estimation will be employed to account for within-subject correlation of repeated measures [56].

Summary measures (e.g., means, frequencies, proportions, incidence rates) and effect estimates (i.e., regression coefficients) will be reported as point estimates and 95 % confidence intervals. In general, risk ratios with corresponding CIs will be used to compare dichotomous outcomes across trial groups (e.g., prevalence of SGA), and differences in means will be used for between-group comparisons of continuous variables. *P* values will be reported to three decimal places, with *P* values less than 0.001 reported as less than 0.001. Statistical analyses will be performed using the STATA software package (StataCorp, College Station, TX, USA) with analyses of primary trial outcomes performed in a blinded fashion. Plans of analysis to address secondary objectives will be presented elsewhere.

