### Design and sample size

The MDIG trial is a randomized, placebo-controlled, double-blinded, dose-ranging trial with a 1:1 allocation ratio across five parallel groups (Fig. 1). A total of 1300 pregnant women will be randomized, with a target of allocating 260 women in each group (Fig. 1). The primary outcome analysis will be a between-group comparison of mean LAZs at 1 year of age, assuming up to 15 % attrition from each group before this time point. To assess the effect of prenatal vitamin D, we plan to perform five primary between-group analyses, comprising each vitamin D dose versus placebo (three comparisons) and comparisons between adjacent doses (two comparisons). A conservative approach to addressing multiple testing is to partition the α (risk of type I error) among the five comparisons (conventional overall 0.05 divided by 5); thus, each between-group comparison will be tested as a two-sided test with an α of 0.01, assuming 90 % power. With 220 analyzable participants per group (about 85 % of total enrolled), the minimum detectable difference in LAZ will be 0.40 z-score units, which equates to approximately 1.0 cm at 1 year of age based on WHO growth standards. In our preliminary trial, we observed an increase in LAZ of 0.44 at 1 year attributable to prenatal vitamin D supplementation, which corresponded to an increase of 1.1 cm (95 % CI, 0.06–2.0), adjusted for sex [26].

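### Holm is valid for the five prenatal comparisons, but several of its thresholds after the first rejection are stricter than the stated overall α of 0.05 requires; a rejection-dependent Shaffer step-down recovers a modest amount of power

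*Protocol article*

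**What the plan says.** Both the Design and sample size section and the Statistical analysis section define the same family of five prenatal comparisons. The latter lists them as "each prenatal vitamin D dose versus placebo (three pairwise comparisons), as well as comparisons between all adjacent vitamin D doses (two pairwise comparisons"), says that "an overall α for statistical significance for all five comparisons will be 0.05 (two-sided"), and adds that "the Holm test will be used to account for multiple testing". The sample size section divides α equally: "each between-group comparison will be tested as a two-sided test with an α of 0.01, assuming 90 % power". It then gives the resulting precision: "With 220 analyzable participants per group (about 85 % of total enrolled), the minimum detectable difference in LAZ will be 0.40 z-score units". That section itself describes splitting α among the five comparisons as conservative. Neither section mentions the logical relations among the five hypotheses. The procedure is named for the primary outcome, so this is a choice the article fixes and not a detail left to another document.

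**The concern.** Holm works for any set of hypotheses because it assumes nothing about how they relate. Here they are closely related. If placebo equals 4200 and 4200 equals 16,800, then placebo equals 16,800 as well. A procedure that ignores such links can demand a smaller p-value than the stated 5% family-wise error requires.

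The effect falls on comparisons tested after the first rejection. For example, suppose 16,800 IU/wk versus placebo is rejected first and another comparison has p = 0.020. Holm requires 0.05/4 = 0.0125 and declares it non-significant. The same overall α already permits rejection at 0.05/2 = 0.025. The Vitamin D doses section and the Discussion present the trial as a study of dose–response, so conclusions about the second and third comparison matter, not only the first.

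**Working it through.** **Inputs from the article.** Five comparisons, overall two-sided α 0.05, Holm (Statistical analysis). 220 analysable per group, per-comparison α 0.01, power 90%, detectable difference 0.40 LAZ (Design and sample size). Postpartum detectable difference 0.31 at α 0.05 (same section).

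**Assumption: SD of LAZ.** None is stated, so it is solved from difference = (z₁₋α/₂ + z₀.₉₀) × SD × √(2/220).
- Prenatal: (2.576 + 1.282) × 0.0953 = 0.368 per unit SD, so 0.40 implies SD = 0.40/0.368 = 1.09.
- Postpartum: (1.960 + 1.282) × 0.0953 = 0.309 per unit SD, so 0.31 implies SD = 1.00.

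Both values are used below.

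**The plan's own figure.** 0.05/5 = 0.01, as stated. This is also Holm's first threshold.

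**How many nulls can be true together.** Write P, A, B, C for the means under placebo, 4200, 16,800 and 28,000. The five nulls are P=A, P=B, P=C, A=B, B=C. Going through all 15 ways to group four means into equal sets, the number of true nulls is 0, 1, 2, 3 or 5, never 4.

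**Thresholds.** At each step, divide 0.05 by the largest number of nulls that can all be true given those already rejected (Shaffer's S2 rule).

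| Step | Holm | Rejection-dependent Shaffer |
|---|---|---|
| 1 | 0.05/5 = 0.0100 | 0.0100 |
| 2 | 0.05/4 = 0.0125 | 0.05/3 = 0.0167; 0.05/2 = 0.0250 if P=B was rejected first |
| 3 | 0.05/3 = 0.0167 | 0.0250 after 8 of 10 pairs; 0.0167 after {P=A, A=B} or {P=C, B=C} |
| 4 | 0.05/2 = 0.0250 | 0.0500 after 6 of 10 triples; 0.0250 after the other four |
| 5 | 0.0500 | 0.0500 |

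Two checks on the table: once P=B is false, A can equal only one of P and B, and so can C, so at most two other nulls are true. After rejecting P=A and A=B, P=B=C is still possible, which leaves three.

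**Why the error rate is kept.** Just before the first wrong rejection, every null already rejected is false. The true nulls therefore number no more than the divisor m in use. A wrong rejection needs some true null to have p ≤ 0.05/m, which by Bonferroni has probability at most 0.05. Each divisor is no larger than Holm's, so every Holm rejection is retained.

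**Size of the gain.** Simulation with 220 per group and two-sided z tests, Holm to S2; effects are for 4200/16,800/28,000 versus placebo. Independent runs agreed to within about 1 point.

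| True effects | SD | All three doses differ from placebo | Power per dose-versus-placebo comparison |
|---|---|---|---|
| 0.4/0.4/0.4 | 1.00 | 91.7% to 94.0% | about 96.2% to 97.2% |
| 0.4/0.4/0.4 | 1.09 | 83.7% to 87.6% | about 92.2% to 94.0% |
| 0.3/0.3/0.3 | 1.00 | 56.5% to 62.9% | about 75% to 79% |
| 0.3/0.3/0.3 | 1.09 | 45.6% to 52.4% | about 66–67% to 70–71% |
| 0.2/0.3/0.4 | 1.09 | 28.2% to 34.0% | 31.8% to 37.0%; 66.0% to 69.9%; 90.6% to 91.7% |

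The chance of at least one rejection is identical under both procedures (for example 98.4% at 0.4/0.4/0.4, SD 1.09), because step 1 is the same. Simulated family-wise error was about 5% or less throughout; the largest value, 5.05%, was the same under Holm and within simulation error.

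**The case against.** The strongest reply is that nothing in the article is wrong. Holm is a standard, pre-specified test with strong control at 5%, and the article openly accepts a conservative approach. That stands: this is an efficiency point, not an error-rate fault.

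Two stronger readings are tempting and not supported. A reader might infer that the trial is underpowered or that its sample size should change. It should not: every comparison was sized at α 0.01, Holm's strictest step, which stays the same. A reader might also infer that all of Holm's later thresholds are too strict. Step 5 never changes, step 3 is unchanged after two pairs of rejections, and step 4 after four triples.

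The size also needs care. The article does not make separating all three doses from placebo its success criterion; it plans five pairwise analyses. Per comparison the gain is smaller: 1 to 2 points when all doses have the planned 0.40 effect, and under 1 point where power is already about 95%. Nearly all of the all-three-doses gain needs the rejection-dependent version. Shaffer's simple fixed divisors (5, 3, 3, 2, 1) move that probability only from 83.8% to 83.9% at 0.4/0.4/0.4 and from 45.8% to 46.1% at 0.3/0.3/0.3 (SD 1.09).

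Preferring one fixed ladder for transparency is a legitimate choice. What remains is that the alternative never loses a Holm rejection, keeps the same error guarantee, and sometimes reaches a conclusion that Holm withholds.

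**Conclusion.** The point holds as a modest improvement to a valid analysis. The impossibility of exactly four true nulls, and the thresholds that follow, are exact and need no assumption about SD, effect size or whether the two arms given 28,000 IU/wk prenatally are pooled. The size of the gain does depend on assumptions: with 220 per group, SD 1.00 to 1.09 and the effects shown, it is about 1 to 6 points per dose-versus-placebo comparison and about 2 to 7 points for all three doses together. Error control, the planned 0.40 detectable difference, the chance of any rejection, and the estimates with their confidence intervals are unaffected.

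**What to change.** In the Statistical analysis section, replace the Holm test with Shaffer's rejection-dependent (S2) step-down test at overall two-sided α 0.05, and list these thresholds before unblinding:

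- Step 1: 0.05/5.
- Step 2: 0.05/3, or 0.05/2 if 16,800 versus placebo was rejected first.
- Step 3: 0.05/2, except 0.05/3 after {4200 vs placebo, 4200 vs 16,800} or {28,000 vs placebo, 28,000 vs 16,800}.
- Step 4: 0.05, except 0.05/2 after {all three doses vs placebo}, {4200 and 16,800 vs placebo, 28,000 vs 16,800}, {16,800 and 28,000 vs placebo, 4200 vs 16,800} or {16,800 vs placebo, both adjacent-dose comparisons}.
- Step 5: 0.05.

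The S2 version must be named explicitly, since the fixed-divisor version brings little. The change takes one sentence and a short table, and needs no participants, data or new sample size. Its cost is that the threshold depends on which comparisons were already rejected, which is harder to explain than one fixed ladder. Enrolment was still open at publication and the analysts are blinded, so it can be made without any knowledge of results.

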### Objectives

The primary aims of the trial are to estimate (1) the effect of maternal prenatal oral vitamin _D3_ supplementation (4200 IU/wk, 16,800 IU/wk, or 28,000 IU/wk administered as weekly doses) versus placebo on infant length at 1 year of age in Dhaka, Bangladesh; and (2) the effect of maternal postpartum oral vitamin D_3_ supplementation (28,000 IU/wk) versus placebo on length at 1 year of age among infants born to women who received vitamin D 28,000 IU/wk during pregnancy. Secondary anthropometric outcomes include birth size and the prevalence of SGA, the prevalence of stunting at 1 year of age, and mean attained LAZ and stunting prevalence at 2 years of age.

Clinical, biochemical, and microbiological surveillance of enrolled mother-infant pairs will enable a range of secondary objectives to be addressed, including (1) estimation of the effect of maternal vitamin D supplementation on the incidence of acute respiratory infections (ARIs) during early infancy; (2) exploration of the roles of specific hormones, nutrients, environmental contaminants, and inflammatory markers in the mediation or modification of the effect of vitamin D on fetal and infant growth, with particular emphasis on the role of the parathyroid hormone (PTH) system; and (3) investigation of the role of epigenetic modification of genes involved in perinatal vitamin D metabolism in infant stunting.

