POC tests include blood pressure measurement, urine dipstick testing, and Hb concentration estimation. Maternal systolic and diastolic blood pressure is measured using an automated digital blood pressure monitor (WatchBP Home; MicroLife USA, Clearwater, FL, USA). Two readings are taken at least 1 minute apart and recorded; if either diastolic or systolic measurements differ between the paired readings by more than 10 mmHg, a third measurement will be performed. For analysis, paired readings will be averaged; where a third reading has been obtained, the single discordant reading will be excluded. Urine dipsticks (Urinalysis Reagent Test Strips; Siemens Diagnostics, Erlangen, Germany) are used at enrollment as part of the eligibility assessment and then after enrollment if high blood pressure is detected (systolic blood pressure ≥140 mmHg and/or diastolic blood pressure ≥90 mmHg) or if there are symptoms (e.g., dysuria) suggestive of urinary tract infection (to test for leukocyte esterase). Maternal Hb will be measured at enrollment (as part of the eligibility screening process) in a finger-stick blood sample using a handheld hemoglobinometer (Hb 201; HemoCue, Ängelholm, Sweden). Infant Hb is measured using the same HemoCue device at 6 months of age.

Standardized procedures for infant length, weight, and head circumference (HC) measurements were adapted from the INTERGROWTH-21st study standard operating procedures [46]. Other published resources were adapted to develop standard protocols for measurement of upper arm length (UAL) [47], mid-upper arm circumference (MUAC) [48], and rump-to-knee length (RKL) [49]. Infants are measured independently by two study personnel at each visit. The paired measurements are compared, and if they differ by more than the threshold values (7 mm for length; 5 mm for HC, UAL, MUAC, and RKL; and 50 g for weight), a second set of measurements is performed. If the second pair of measurements differs by more than the threshold values, the procedure is repeated a third time (except for infant weight, which is measured using a digital scale and thus expected to be concordant). Length, weight, and HC are measured at birth, at one randomly assigned weekly visit during the first 2 months after birth, and then every 3 months starting at the 3-month visit. MUAC, UAL, and RKL are measured at 3, 6, 12, and 24 months; UAL and RKL are also measured at birth.

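### The primary postpartum comparison leaves out birth length and gestational age at birth, which are valid covariates for that contrast; this costs precision but causes no bias

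*Protocol article*

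**What the plan says.** The second primary aim (Objectives) concerns the postpartum supplement "among infants born to women who received vitamin D 28,000 IU/wk during pregnancy". Both arms of this contrast therefore have the same prenatal assignment. Under Randomization and allocation concealment, allocation is masked and each participant's pack holds her prenatal and postpartum vials together.

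The Statistical analysis section describes the prenatal comparisons first: "each analysis will be akin to an independent-samples" t test. It then analyses the postpartum effect "using a statistical approach similar to that described for the prenatal effect analysis". All primary analyses are run "without adjustment for baseline covariates, and also without imputation for missing data". The only planned covariate adjustment is a sensitivity analysis chosen by observed imbalance: "Multivariable adjustment will be used for covariates that substantially differ across groups at baseline".

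Birth size is on the measurement schedule (Data collection procedures): "Length, weight, and HC are measured at birth, at one randomly assigned weekly visit during the first 2 months after birth". Gestational age at birth is also available, because the article plans age-corrected z-scores for preterm infants and a subgroup analysis by gestational age.

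Design and sample size gives a minimum detectable difference (MDD) of 0.31 z-score units for the postpartum contrast, with 220 infants per group, 90% power and two-sided α of 0.05.

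**The concern.** The same rule is applied to two contrasts for which birth size plays different roles. In the prenatal comparisons birth length lies downstream of treatment, and adjusting for it could remove part of the effect being estimated. In the postpartum comparison the arms first differ after delivery, so birth length and gestational age at birth act as baseline variables even though they are recorded after randomization.

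An infant's length at birth can be expected to predict length at 1 year to some degree. Leaving it out of the primary model leaves explainable variance in the error term. What is at stake is the width of the confidence interval and the power for one of the two primary aims. The validity of the test is not in question.

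**Working it through.** **Inputs from the article.** n = 220 per group, two-sided α = 0.05, power 90%, MDD 0.31 (Design and sample size). Neither the SD of 1-year LAZ nor its correlation r with birth LAZ is given. Both are therefore assumptions, and r is run from 0.2 to 0.6.

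**Reproducing the stated figure.** MDD = (1.960 + 1.282) × SD × √(2/220). With SD = 1.0 this is 3.2415 × 0.0953 = 0.309, which matches 0.31. Power for 0.31 is 90.2% (90.0% by the noncentral t), and the required n is 219 per group. The sample size thus assumes an unadjusted comparison with SD 1.0 and takes no credit for a covariate.

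**Effect of adjustment, complete birth data.** ANCOVA multiplies the standard error by √(1 − r²). With SD 1.0:

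| r | Reduction in SE | MDD | Power for 0.31 |
|---|---|---|---|
| 0 | 0% | 0.309 | 90.2% |
| 0.2 | 2.0% | 0.303 | 91.3% |
| 0.3 | 4.6% | 0.295 | 92.6% |
| 0.4 | 8.3% | 0.283 | 94.4% |
| 0.5 | 13.4% | 0.268 | 96.4% |
| 0.6 | 20.0% | 0.247 | 98.2% |

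A simulation with 220 per arm, a true difference of 0.31 and 4,000 runs per setting gave reductions of 7.6% at r = 0.4 and 20.2% at r = 0.6. The mean adjusted estimates were 0.309 and 0.311, so adjustment introduced no visible bias.

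**Missing birth lengths.** The article does not state how complete they will be; 20% missing is an assumption.
- If these infants stay in the model through mean imputation of the covariate plus a missing indicator, the factor is √(1 − 0.8r²). The reduction is then 1.6% at r = 0.2, 3.7% at r = 0.3, 6.6% at r = 0.4 and 15.6% at r = 0.6.
- If they are dropped, the factor is √(1 − r²)/√0.8. The standard error then rises by 2.5% at r = 0.4 and falls by 10.6% at r = 0.6. In general, dropping cancels the gain once the missing share reaches r²: 16% at r = 0.4 and 36% at r = 0.6.

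**Sensitivity to the SD.** The prenatal MDD of 0.40 at α = 0.01 implies SD = 0.40/0.3678 = 1.09. The pilot interval of 0.06–0.82 in 134 infants (Background) gives SE = 0.76/(2 × 1.96) = 0.194 and, assuming equal arms, SD = 0.194/√(4/134) = 1.12. At SD 1.1 the postpartum MDD is 0.340 and power for 0.31 is 84.0%. With adjustment that power would be 89.7% at r = 0.4, 92.7% at r = 0.5 and 95.9% at r = 0.6.

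**Whether another planned analysis supplies the gain.** The spline models of change in LAZ are secondary. With equal variances at both ages, a change score has variance 2(1 − r) times that of 1-year LAZ, which is larger than the unadjusted variance whenever r < 0.5. At r = 0.6 its SD factor is √0.8 = 0.894, against 0.800 for ANCOVA.

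**The case against.** The strongest reply is that nothing here is wrong. The unadjusted analysis is openly prespecified, unbiased and consistent with its own sample-size statement, so preferring ANCOVA is only a preference for efficiency. That is correct as to validity, and the point claims no more.

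Second, the gain rests on an r that the article does not give, and the article offers reasons to expect a lower value. The first length board often lost calibration and was replaced on 15 December 2014 (Data collection procedures). Perinatal data from births outside the study facility are collected only where feasible (Visit schedule). The growth standard comes from a full-term cohort, so birth z-scores of preterm infants are distorted. These points stand: they reduce the gain, and they are why the low end of the range is shown. Under masking they do not bias the adjusted estimate.

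Third, a reader might infer that birth size is ignored altogether. It is not: the spline models, the gestational-age-corrected sensitivity analysis and the gestational-age subgroup analysis all draw on birth information. Only the primary model omits it.

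Fourth, the fix is not wholly free. The two aims would use different models, and covariate imputation sits awkwardly with a primary analysis defined as having none. The article explains that rule in terms of missing 1-year LAZ, however, so filling in a covariate does not change which infants are analysed. The timing of the birth measurement relative to the first postpartum tablet is also not stated, and it needs to be.

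**Conclusion.** The point holds as a loss of efficiency on one of the two primary aims. Birth length and gestational age at birth are legitimate covariates for the postpartum contrast alone, are already collected, and are left out because the prenatal approach was carried over.

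With complete birth data the reduction in standard error is about 2–5% at r = 0.2–0.3 and 8–20% at r = 0.4–0.6. In the latter range, at SD 1.0, the MDD falls from 0.31 to 0.28–0.25. With 20% of birth lengths missing and a missing indicator, the reduction is about 7–16% at r = 0.4–0.6. All of this rests on an assumed r.

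Two stronger readings are not supported. One is that 8–20% of the standard error is definitely being lost: the article gives no correlation, and the gain may be much smaller. The other is that the comparison is underpowered or invalid as planned: it reaches its stated 90% power for 0.31 if the SD is 1.0. The larger SDs implied by other figures in the article make extra precision more useful, but they raise a separate question about the sample-size inputs and do not make an unadjusted analysis wrong.

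**What to change.** For the postpartum contrast only:

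- Prespecify as primary an ANCOVA of 1-year LAZ on group, birth length (or birth LAZ) and gestational age at birth.
- Keep infants without a birth length by imputing the covariate mean and adding a missing indicator. State that this is an exception to the no-imputation rule and applies to the covariate, not to the outcome.
- State that birth length is to be measured before or close to the first postpartum dose, so that it can be treated as preceding the contrast.
- Report the unadjusted difference as a sensitivity analysis.

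Leave the prenatal comparisons unadjusted for birth size, since it may be affected by the prenatal dose.

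The cost is analysis wording and no new data collection. The small downsides are a different model for each primary aim and a gain that shrinks with missing birth lengths or lengths taken on the earlier board.
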